**Methods:**

The current trial is a multicenter, randomized, three-arm controlled study undergoing in China. About 243 people who aged from 18 to 65 years with FC will be recruited in this study. These participants will be randomly allocated into three treatment groups, including electro-acupuncture (EA), Mosapride (M) and Mosapride & Sham Electro-acupuncture (MS) groups in a 1:1:1 ratio. Both the EA and sham EA receives 16 sessions of needling at Quchi (LI11) and Shangjuxu (ST37) during 4 weeks of treatment, and a follow-up period of 4 weeks. These groups will be compared on the primary outcomes of the number of times of defecation at baseline and 2, 4, 8 weeks after randomization. The secondary outcome measures include: stool consistency, intensity of defecating difficulty, MOS item Short Form health survey (SF-36), Self-Rating Anxiety Scale (SAS), Self-rating Depression Scale (SDS), and the validated Patient Assessment of Constipation Quality of Life (PAC-QOL). These outcomes are measured at baseline and 2, 4 weeks after randomization, but SF-36 is measured at baseline and 4 weeks after randomization.

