## Methods and Design

### Design

This is a multicenter randomized controlled, three-arm trial enrolling both men and women with functional constipation in China. This study will be conducted at Tongji Hospital affiliated to Tongji Medical College, Huazhong University of Science and Technology; Hubei Provincial Hospital of TCM; Hospital of Huazhong University of Science and Technology. Tongji Hospital is the central structure of the study. The participants will be allocated through complete randomization in a 1:1:1 ratio. The randomization sequence will be generated using R2.0 software. A designated researcher will prepare the assignments in opaque envelopes in sequence. The acupuncturists will only know of the group assignment prior to the treatment.

This trial is financed by the National Basic Research Program (No. 2011CB505203). The research protocol has been approved by the Clinical Trial Ethics Committee of Tongji Medical College, Huazhong University of Science and Technology (approval no. FWA00007304) and registered on the ClinicalTrials.gov protocol registration system (
http://clinicaltrials.gov/ct2/show/NCT01781897, ClinicalTrials.gov ID: NCT01781897).The duration of this study is 9 weeks for each patient: a screening period of 1 week, a treatment period of 4 weeks, and a follow-up period of 4 weeks. Constipation diaries are required to record at least 1 week before randomization as baseline data and this course will be continue to 8 weeks if they are eligible for this trial. All outcomes are assessed at baseline and 2, 4, and 8 weeks after randomization according to the diaries. A total of 16 sessions of acupuncture treatment will performed over a period of 4 weeks and each session will last 30 min after randomization. Five times a week in the first 2 weeks and three times a week in the last 2 weeks (Figure 
1).

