### Outcome measures

The primary outcomes of the study is the times of defecation per week at baseline and at the 2nd, 4th and 8th week after randomization. Secondary efficacy end points include: 1) stool consistency
[10]; 2) intensity of defecating difficulty; 3) MOS item Short Form health survey (SF-36)
[11]; 4) Self-Rating Anxiety Scale (SAS)
[12]; 5) Self-rating Depression Scale (SDS)
[13]; 6) the validated Patient Assessment of Constipation Quality of Life (PAC-QOL)
[14] (Table 
1).

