### Sample size calculation

Sample size was determined based on a study
[15] where the average defecation rate of patients with functional constipation was 2.6 times per week with a standard deviation of 2.2 after drug treatment, and a 1.4-fold difference in the clinical effects between the drug and the placebo is considered to be of clinical relevance. In this study, we anticipated that an improvement of the mean defecating frequency is 4.0 after acupuncture treatment, with a standard deviation of 3. To detect this difference, we need a sample size of 71 in each group (α = 0.05, β = 0.10)
[16]. To allow 15% for loss to follow up, our proposed trial requires 243 patients (81 for each group).

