### Statistical analysis

Statistical analysis of all data will be done by the Department of Epidemiology and Biostatistics, School of Public Health, Tongji Medical College, Huazhong University of Science and Technology, which is blinded to this trial. SPSS 17.0 software packages will be used to analyze the data. All data are provided as mean ± standard deviation (SD) in continuous data and as frequency/percentage in categorical data. All of the analyses will be based on both an intention-to-treat analysis (ITT) and a treated-per-protocol analysis (TPP). The intention-to-treat (ITT) population was defined as the patients who are randomized and received at least one treatment session. The missing data will be dealt with the last observation value carried forward (LOCF) method. The per-protocol (PP) population was defined as the patients who have no major protocol violations in the ITT set. Both results of analysis will be compared to check whether the results are consistent.

Comparisons among baseline characteristics in different groups will be analyzed at first by analysis of variance, Chi-square test, and others. Then analysis will be applied to compare the effects of intervention between groups. Chi-square test will be used for comparison of categorical variables and analysis of variance of repeated measures will be performed for continuous parameters between the groups. The level of significance was set a P value less than 0.05.

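### The repeated-measures ANOVA does not fix which term or visit answers the primary question or how baseline enters, and neither usual reading estimates the single 1.4-per-week difference used for sizing

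*Protocol article*

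**What the plan says.** The Outcome measures section defines the primary outcome as "the times of defecation per week at baseline and at the 2nd, 4th and 8th week after randomization". The abstract does the same, comparing the groups on the "primary outcomes of the number of times of defecation at baseline and 2, 4, 8 weeks after randomization". Baseline is therefore written in as one of the outcome's time points.

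The Design section gives "a treatment period of 4 weeks, and a follow-up period of 4 weeks", so weeks 2 and 4 fall in the treatment period and week 8 comes four weeks after it ends. It also states that "Constipation diaries are required to record at least 1 week before randomization as baseline data".

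For continuous outcomes, the Statistical analysis section names one method: "analysis of variance of repeated measures will be performed for continuous parameters between the groups". It names no model term, contrast or primary visit. The only use of baseline that it states is "Comparisons among baseline characteristics in different groups will be analyzed at first by analysis of variance, Chi-square test, and others".

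The Sample size calculation section works from one pair of post-treatment values: "2.6 times per week with a standard deviation of 2.2 after drug treatment", and "an improvement of the mean defecating frequency is 4.0 after acupuncture treatment, with a standard deviation of 3". The difference is 4.0 − 2.6 = 1.4 per week.

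**The concern.** A repeated-measures ANOVA with three arms and several visits yields two tests that could be called the treatment comparison: the group main effect and the group-by-time interaction. They answer different questions, and neither is the one for which the trial was sized.

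The main effect compares each arm's average over the visits in the model. If baseline is one of them, a visit whose expected difference is zero by randomisation is averaged in, and so is a visit four weeks after treatment. The interaction asks whether the arms' profiles over time differ in any way. With three arms and four visits it has (3 − 1) × (4 − 1) = 6 df, and a significant result does not say by how much, or at which week, acupuncture differs from either control.

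At stake are power on the first reading and, on the second, an interpretable estimate of the effect. Because the text does not choose, two P values could be offered against the single 0.05 threshold.

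**Working it through.** **Inputs from the protocol article.** SDs 2.2 and 3, difference 1.4, 71 evaluable per arm, α = 0.05, power 90% (Sample size calculation); visits at baseline and weeks 2, 4 and 8 (Outcome measures).

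**Assumptions, because the document gives no figures.** Two-sided test; the same variance at every visit; equal correlation r between any two visits, taken as 0.3, 0.5 and 0.7; effect of 1.4 at weeks 2 and 4, and at week 8 either 1.4 (sustained) or 0 (lost).

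**1. The plan's own figure.** n = 2·SD²·(1.96 + 1.2816)²/1.4². With the simple mean SD of 2.6, n = 72.5, so 73, close to the stated 71; power at 71 is 89.4%. With the average variance s² = (2.2² + 3²)/2 = 6.92 (SD 2.63), n = 75 and power at 71 is 88.7%. The rest uses 6.92. The sizing is thus an unadjusted two-group comparison at one time point.

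**2. Group main effect with baseline as a level (acupuncture versus mosapride).** The difference in four-visit means is (0 + 1.4 + 1.4 + 1.4)/4 = 1.05 if sustained, and (0 + 1.4 + 1.4 + 0)/4 = 0.70 if lost. The variance of a four-visit mean is s²(1 + 3r)/4, and power is Φ(d/√(2·var/71) − 1.96).

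| r | variance | SE | power, d = 1.05 | power, d = 0.70 |
|---|---|---|---|---|
| 0.3 | 3.287 | 0.304 | 93% | 63% |
| 0.5 | 4.325 | 0.349 | 85% | 52% |
| 0.7 | 5.363 | 0.389 | 77% | 44% |

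**3. Group-by-time interaction, three arms, 6 df.** Assume equal means in the two mosapride arms. The noncentrality is 71·Σ(interaction effects²)/(s²(1 − r)), with 6 and 3 × (213 − 3) = 630 df. The sum of squares is 0.98 if sustained and 1.307 if lost. At r = 0.5 the noncentrality is 71 × 0.98/3.46 = 20.1 or 71 × 1.307/3.46 = 26.8.

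| r | power, sustained | power, lost by week 8 |
|---|---|---|
| 0.3 | 82% | 93% |
| 0.5 | 94% | 99% |
| 0.7 | 99.7% | >99.9% |

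**4. Week 4 ANCOVA on baseline.** The variance is s²(1 − r²): 6.297, 5.190 and 3.529. With d = 1.4 the SEs are 0.421, 0.382 and 0.315, and power is 91%, 96% and 99%, whatever happens at week 8. The unadjusted week 4 comparison has 89%.

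**The case against.** A reader might infer that the plan does treat baseline as an outcome, dilutes the effect and wastes the baseline. The text does not establish this. It names neither the tested term nor the levels of the repeated factor, and listing baseline among the measurement times does not make it a level in the model. The interaction uses baseline through within-patient contrasts, and a fading effect raises its power. If the factor is weeks 2, 4 and 8 only, which the text allows, the sustained-effect main test has 99/97/94% power. Even the four-visit main effect is not always worse: with a sustained effect and r = 0.3 its 93% exceeds the 89% of an unadjusted week 4 comparison and slightly exceeds the 91% of week 4 ANCOVA. All of this stands, so dilution and loss of power can be claimed only conditionally.

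A reader might also infer an inflated type I error from pooling unequal SDs. That would need a pairwise contrast tested with error pooled over three arms, which the plan does not state; the point is not made here.

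It can also be said that an article leaves model terms and covariates to a fuller document. Silence alone would be no finding. What remains is a mismatch between things the article does state: the outcome's time points, the one named method, and a sample size built on a single difference. The sizing text names no week, so week 4 is an example of a matching contrast, not a reading of the plan.

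**Conclusion.** The concern holds in conditional form. The stated analysis does not settle which term answers the primary question, and neither usual term, with baseline in the repeated factor, estimates the 1.4-per-week difference behind the sample size.

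- Main effect over four visits: the tested difference is 25% smaller (1.05) or 50% smaller (0.70). Power falls below 90% at r = 0.5 and 0.7 if the effect lasts, and at all three correlations if it is gone by week 8.
- Interaction: power falls short of 90% only for a sustained effect at r = 0.3. The weakness is the absence of an effect estimate at any week.

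These sizes rest on the assumed correlations, equal variances across visits, the assumed week 8 effect and, for the interaction, equal means in the two mosapride arms. The gain from baseline adjustment shrinks at low correlation: at r = 0.2 week 4 ANCOVA has 89.9% against 88.7% unadjusted. This is an improvement that should be made; it does not show that the trial is underpowered.

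**What to change.** In the Statistical analysis section, take weeks 2, 4 and 8 as outcomes and baseline weekly defecations as a covariate, in a longitudinal mixed model with arm-by-visit means or in an ANCOVA. Name one primary visit and contrast that matches the post-treatment difference used for sizing, for example week 4, and report it with a 95% CI. In the Outcome measures section and the abstract, describe baseline as the reference measurement and not as one of the outcome's time points.

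The cost is wording only. The pre-randomisation diary is already required, so no extra patients, visits or data are needed. Recruitment is under way, so the change should be fixed and dated before any outcome data are seen by arm.

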### Quality control

In order to guarantee the quality of trial, all acupuncturists are asked to attend special training. The training includes how to fill in the case report form, how to manipulate both true and sham needles, how to teach the patients to take Mosapride Citrate tablets, and other details of this trial. A special training test will be given to the acupuncturists to ensure their understanding of protocol. After passing the test they are qualified to perform this trial. Only acupuncturists will know the grouping scheme and all the researchers are forbidden to alter the assignment. Inspectors from the central structure of the study will check each research center monthly and report to the investigator. Reasons and details of drop-outs or withdrawals will be documented.

## Discussions

According to TCM theory, the body was regarded as a whole composed of internal and external organs. These organs connected with each other by special ways called meridians, in which "qi" and "blood" is circulating. Disease is a state that "qi" and "blood" is deviated from balance. Functional constipation could be attributed to "defecation difficulty" in traditional Chinese Medicine (TCM), which were considered to be caused by improper diet, emotional disturbance, and invasion of exogenous pathogen. According to the different pathogenic factors, "defecation difficulty" could be classified into the categories of "Qi-deficiency constipation", "Blood-deficiency constipation", "Yin-deficiency constipation", and "Qi-deficiency constipation" etc. These disturbances attributed to dysfunction of large intestinal transit function and insufficient large intestinal liquid.

Chinese medicines, acupuncture and moxibustion as effective complementary and alternative medicine (CAM) have been widely used to treat FC in China and clinically adopted in the western world
[17]. Acupuncture has been believed to treat FC at least 3000 years. Some studies have indicated that acupuncture can play a therapeutic role in Functional gastrointestinal (GI) symptoms through alter acid secretion, GI motility, and visceral pain
[18–21]. However, the literature which has been made to investigate the efficacy of acupuncture on function constipation is scarce. Some pilot studies reported that acupuncture could improve symptoms of constipation but did not set a control group
[22, 23]. In another study, acupuncture has been found to increase the frequency of bowel movement in 17 children with chronic constipation during a 10-week treatment period but not include adult patients
[24]. Based on the current evidences from clinical trials, acupuncture seems show potential for treating constipation. However, this deduction is insufficient and may lead to bias because the poor quality without a standardized acupuncture protocol. Therefore we designed a multicenter randomized controlled protocol and expected to provide convincing evidence to clarify the efficacy of acupuncture for treating FC.

Acupoints selected in this trial were Quchi (LI11) and Shangjuxu (ST37), which were He-Sea and Lower He-Sea points of Large Intestine meridians. According to traditional acupuncture theories, both of them have a positive therapeutic effect in treating internal organ disease. Differing from the other studies adopted non-acupoints in placebo control, we will use a validated placebo needling
[9] and special electrode lines with no current output at the same acupoints to mimic as closely as possible the real situation on patients. In the other hand, to avoid communication with each other, patients will be assigned to acupuncture treatments alone at different times. In addition, we will use mosapride as a positive control group because it has been confirmed as an effective drug to treat FC in China and western countries. The primary outcome assessment will be collected from the diaries which will be convenient and easy for patients to record. Certainly, the safety of interventions is needed to consider during the whole process.

As far as we know, this is the first acupuncture trial adopting sham EA combined with mosapride (MS) as a control to observe the efficacy of acupuncture for treating FC. The reasons we selected mosapride & sham acupuncture as a control instead of simple placebo acupuncture based on: Firstly, it will help to improve therapy compliance and reduce the rate of drop-out so as to ensure that the study is completed smoothly, because a big part of patients expect to receive acupuncture treatment when they participate in this trial. Second, whether simple placebo acupuncture is effective for patients with functional constipation is controversial, so it accords with the ethical principles of beneficence and justice to avoid ethical confusion.

However, some limitations we must also recognize that patients are not blinded in this trial. The participants will know whether they receive acupuncture or medication although they will not know true or sham acupuncture they will receive. And then, the physiological effects may be amplified when patients have a higher positive beliefs and expectations of benefit of acupuncture compared with medicine, which will impact the acupuncture effect. These factors will lead to a bias of the outcome assessment. In conclusion, the study will supply significant evidence for using acupuncture to treat FC, and help us to observe whether it is a therapeutic effect rather than a placebo effect.

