## Abstract

**Background:**

Functional constipation (FC) is a common functional gastrointestinal disorders (FGIDs) which has a major impact on the quality of life. Acupuncture is widely used as an alternative and complementary medicine (CAM) for FC, but the available evidence of its effectiveness is scarce. Therefore, we will perform a randomized controlled trial to determine whether acupuncture improves symptom and quality of life in FC patients more effectively than sham acupuncture or gastrointestinal prokinetic agent. This article will report the protocol of the trial.

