### Mosapride & Sham Electro-acupuncture (MS) group

The participants appointed to mosapride & sham acupuncture group will be treated with sham acupuncture while orally given Mosapride Citrate tablets (Dainippon Sumitomo pharmaceutical Co.Ltd, Japan). The dose of mosapride is 5 mg three times a day for 4 weeks continuously as the same as mosapride (M) group. In the sham acupuncture intervention, Park sham devices (PSD)
[9] are used, which are purchased from DongBang AcuPrime. Ltd. Co (Marsh Barton, Exeter, UK). It is a non-penetrating needle device with a blunt and retractable needle, a guide tube and a self adhesive pad. The fixed points are bilateral Quchi (LI11) and Shangjuxu (ST37), which are also the same as the treatment group. A precut guide tube which is fixed by a self adhesive pad was slightly depressed down onto the selected point. And then, the blunt sham needle is carefully placed into the guide tube. When pressed, it telescopes into the handle and induces a pricking sensation rather than penetrates the skin. During this process, no twirling lifting and thrusting manipulation is conducted. The sham electro-acupuncture instrument is applied to the needles but the metal inside the wire has been cut off. We set a stimulation frequency of 2/50 Hz and electric current of 0.3 mA but actually, there is no current output and the participants will never know.

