**Intervention**					
Electro-acupuncture (EA) group	16 sessions of electro-acupuncture				
Mosapride (M) group	5 mg mosapride citrate tablet, three times a day				
Mosapride & Sham	16 sessions of sham electro-acupuncture and 5 mg mosapride citrate tablet, three times a day				
Electro-acupuncture (MS) group					

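### The only sham arm also takes mosapride, so no comparison isolates the specific effect of electro-acupuncture that the protocol says it will test

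*Protocol article*

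**What the plan says.** Patients are randomised to "electro-acupuncture (EA), Mosapride (M) and Mosapride & Sham Electro-acupuncture (MS) groups in a 1:1:1 ratio" (Abstract, Methods). The abstract's Background gives the aim as improving symptoms and quality of life "more effectively than sham acupuncture or gastrointestinal prokinetic agent". The abstract's Discussion and the closing lines of the Discussions section both say the trial will "help us to observe whether it is a therapeutic effect rather than a placebo effect".

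The arms are defined under Interventions and in Table 1:
- EA: Table 1 lists only "16 sessions of electro-acupuncture", and neither it nor the EA section describes an active or placebo tablet.
- M: mosapride alone.
- MS: patients "will be treated with sham acupuncture while orally given Mosapride Citrate tablets", with the drug taken "continuously as the same as mosapride (M) group".

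The Discussions section says of mosapride that "it has been confirmed as an effective drug to treat FC in China and western countries". It explains that MS was preferred to sham acupuncture alone for compliance and ethical reasons. On blinding, it admits that patients are not blinded between acupuncture and medication, but adds that "they will not know true or sham acupuncture they will receive". The primary outcome, weekly defecation frequency, is taken from patient diaries.

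**The concern.** To show that an effect is therapeutic rather than placebo, true and sham needling must be compared with everything else equal. Here EA and MS differ in two ways: true versus sham needling, and no drug versus a drug. The two differences pull in opposite directions and cannot be separated.

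Two wrong readings become possible. If EA and MS come out equal, the trial could be reported as finding acupuncture no better than sham, although EA may have a specific effect as large as the drug's. If EA comes out ahead, the result could be reported as sham-controlled, although tablets mark one of the two needled arms and the outcome is self-recorded. In both cases the stated conclusion would go beyond what the data can carry.

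**Working it through.** **Model.** Let m be the untreated mean, E the specific effect of true EA, P the effect of the needling ritual (common to true and sham) and D the effect of mosapride. Under additivity the arms as described give:

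- EA = m + E + P
- M = m + D
- MS = m + P + D

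**Contrasts.**

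- EA - MS = E - D
- MS - M = P
- EA - M = E + P - D

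**Is E identified?** No. Three arm means carry four unknowns. Take any number c, add it to both E and D, and subtract it from m:

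- EA: (m - c) + (E + c) + P, unchanged
- M: (m - c) + (D + c), unchanged
- MS: (m - c) + P + (D + c), unchanged

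The same three means therefore fit every value of E, and more patients do not help. P and E - D are estimable; E alone is not. A fourth arm (sham alone, or EA with mosapride) would make E estimable. That is noted only to locate the gap and is not proposed.

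**The plan's own figure.** Sample size calculation: means 4.0 (SD 3) after acupuncture and 2.6 (SD 2.2) after drug, difference 1.4, alpha 0.05, beta 0.10, 71 per group. The formula n = 2(1.96 + 1.2816)² SD²/1.4² gives 73 with the averaged SD of 2.6, and 75 with the root-mean-square SD of 2.63. So 71 is roughly reproduced. The point does not depend on it.

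**Illustration under stated assumptions.** The protocol gives no clear mosapride effect, so D is varied from 0 to 1.4 per week. The value 0.74 arises only if the 1.4-fold figure is read as a drug/placebo ratio: 2.6 - 2.6/1.4 = 0.74. The value 1.4 arises if it is read as an absolute difference. With 71 per arm and SD 2.63, SE = 2.63 × √(2/71) = 0.44. At two-sided 0.05, the chance that EA is significantly above MS is Φ((E - D)/SE - 1.96), and significantly below is Φ(-1.96 - (E - D)/SE).

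| Assumed D | E implied by EA - MS = 0 | EA significantly above MS if E = 1.4 | EA significantly below MS if E = 0 |
|---|---|---|---|
| 0 | 0 | 89% | 2.5% |
| 0.74 | 0.74 | 32% | 39% |
| 1.4 | 1.4 | 2.5% | 89% |

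Here E = 1.4 is simply a chosen value. It is not the planned difference, which compares acupuncture with drug and so is already net of the drug effect. The table shows only that the EA-MS result depends on D as much as on E.

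**Blinding, passages side by side.** Interventions and Table 1 give tablets to one needled arm and describe none for the other: needles alone means true EA, needles with tablets means sham. The Discussions section says needled patients will not know which they receive. Its limitation concerns belief in acupuncture versus medicine and does not mention the tablet cue. Expectation from that cue would favour EA and mosapride would favour MS, so the direction of the net bias is unknown.

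**The case against.** Much can be said for the design.

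- **Deliberate control.** The protocol gives compliance and ethical reasons for adding mosapride to the sham. They justify the choice of arm, which is not challenged here. They do not justify the conclusion drawn from it.
- **Other aims are met.** The protocol also asks whether acupuncture is better than medication, and EA versus M addresses that as an open comparison of two strategies. MS versus M informs on the sham effect. Both points stand.
- **The placebo claim is not wholly untestable.** A reader might infer that the trial can say nothing about a specific effect. That goes too far. Since EA - MS = E - D, finding EA > MS with D at or above zero implies E > 0, a conservative one-directional test, provided effects are additive and blinding to needling holds.
- **Unmasking is not proved.** A reader might infer that the tablets reveal the sham arm to patients. They separate the arms by design, but whether patients can use the cue depends on what they are told, and the consent text is not shown. The protocol also admits non-blinding and outcome bias in general terms, treats patients alone at different times, and records expectation of acupuncture at baseline.
- **No firm size can be given.** A reader might infer that EA versus MS understates the specific effect by 0.74 per week. That rests on one reading of the 1.4-fold figure, which the protocol presents as a threshold of clinical relevance without naming the drug. Expressing it as a share of the planned 1.4 would also be wrong, because that difference is already net of drug.
- **No decision rule is stated.** The protocol does not say a null result would be called placebo. It does, however, promise an answer to the therapeutic-or-placebo question without limiting which results could give one.

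**Conclusion.** Wrong as written. The specific effect of EA, which the abstract and the Discussions section say the trial will distinguish from placebo, is not identified by any contrast among the three arms. This follows from the arms as described and from an additive model; it needs no numerical assumption.

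A null or negative EA-MS result says nothing about whether EA is placebo. A positive one supports a specific effect only if mosapride is not harmful, effects are additive and needled patients stay unaware of true versus sham. The third condition is doubtful but not refuted by the documents. The size of the distortion equals the mosapride effect, which the documents do not fix. The range 0 to 1.4 per week is an illustration only.

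**What to change.** Keep the arms and restate the claims.

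1. Describe EA versus MS as EA compared with mosapride under a similar needling ritual, MS versus M as the sham or ritual contrast, and EA versus M as an open comparison of two strategies.
2. In the abstract and the Discussions section, remove the claims of superiority to sham and of therapeutic rather than placebo effect. Alternatively, limit them to the case EA > MS and state the assumptions: mosapride not harmful, additive effects, needled patients unaware of true versus sham. Add that a null or negative result is not evidence that EA is placebo.
3. In the limitations, say that EA versus MS may not be patient-blinded, because tablets accompany only the sham needling and the outcome is a diary.
4. Optionally, ask needled patients at the existing week 4 visit which needling they think they had.

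The cost is rewording and a less favourable claim. Treatment, enrolment, sample size and primary outcome do not change. The optional question would miss patients already past week 4, since the first participant was included in March 2012.
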